# Computerised tomography-based planning with conventional total hip arthroplasty versus robotic-arm assisted total hip arthroplasty: study protocol for a prospective randomised controlled trial

**DOI:** 10.1186/s13063-020-04702-7

**Published:** 2020-09-10

## Abstract

**Background:**

Robotic-arm assisted surgery aims to reduce manual errors and improve the accuracy of implant positioning during total hip arthroplasty. The objective of this study is to compare the accuracy of implant positioning, restoration of hip biomechanics, patient satisfaction, functional outcomes, implant survivorship, cost-effectiveness, and complications in conventional manual total hip arthroplasty (CO THA) versus robotic-arm assisted total hip arthroplasty (RO THA). Preoperative pelvic computerised tomography (CT) scans will be used to create patient-specific, virtual, three-dimensional reconstructions for surgical planning in both treatment groups.

**Methods and analysis:**

This prospective randomised controlled trial will include 60 patients with symptomatic hip osteoarthritis undergoing primary THA. Following informed consent, patients will be randomised to CO THA (control group) or RO THA (investigation group) at a ratio of 1:1 using an online random number generator. Observers will review patients at regular intervals for 2 years after surgery to record predefined study outcomes relating to the accuracy of implant positioning, hip biomechanics, postoperative rehabilitation, clinical progress, functional outcomes, cost-effectiveness, and complications. Primary and secondary objectives will be used to quantify and draw inferences on differences in the efficacy of treatment between the two groups. Intention-to-treat and per-protocol population analysis will be undertaken. Intention to treat relates to the allocated treatment (CO THA or RO THA), and per-protocol refers to the actual treatment received by the patient. The following statistical methods will be employed to analyse the data: descriptive statistics, independent *t* test, paired *t* test, analysis of variance, Fisher exact test, chi-square test, and graphical displays. Ethical approval was obtained from the London-Bromley Research Ethics Committee, UK. The study is sponsored by University College London, UK.

**Discussion:**

This study compares a comprehensive and robust range of clinical, functional, and radiological outcomes in CT-planned CO THA versus CT-planned RO THA. The findings of this study will enable an improved understanding of the differences in CO THA versus RO THA with respect to patient satisfaction, functional outcomes, implant survivorship, cost-effectiveness, and complications.

**Trial registration:**

ClinicalTrials.gov NCT04095845. Registered on 19 September 2019

## Background

Total hip arthroplasty (THA) is a highly successful surgical treatment for symptomatic hip osteoarthritis, which is performed in over 70,000 patients per year in the UK [1]. The procedure has well-established middle- to long-term clinical outcomes, and implant survivorship is greater than 90% at a minimum of 10 years’ follow-up [24]. Achieving accurate implant positioning and restoring native hip biomechanics are important technical objectives in THA. Studies have shown accuracy and reproducibility of achieving these surgeon-controlled factors during THA influences postoperative acetabular bone stock, abductor function, joint stability, soft tissue injury, impingement, bearing surface wear, and long-term implant survival [3, 5, 6, 12, 15, 18, 23]. Conventional manual THA (CO THA) uses radiographic templating, surgical alignment guides, and intraoperative landmarks such as the transverse acetabular ligament to help guide acetabular reaming and implant positioning. However, it is reported that only 38–47% of acetabular components are within the desired range of anteversion and inclination with CO THA, and low surgeon volume is a risk factor for inaccurate implant positioning [2, 3, 8, 10]. Suboptimal implant positioning outside of the acceptable safe ranges may lead to increased hip instability, poor restoration of native hip biomechanics, and premature component failure requiring more complex revision surgery [3, 10, 11, 15, 16].

Evolution in surgical technology has led to the development of robotic-arm assisted THA (RO THA), which aims to facilitate preoperative surgical planning, reduce intraoperative errors in bone resection, and improve the accuracy of implant positioning compared to CO THA. Preoperative computerised tomography (CT) scans of the pelvis and proximal femur are used to create virtual three-dimensional reconstructions of the patient’s anatomy. The surgeon uses this patient-specific computer-aided design (CAD) model to map optimal implant positioning to achieve the desired bone coverage, component positioning, hip biomechanics, and correction of any limb-length discrepancy. An intraoperative robotic device with audio, visual, and tactile feedback helps to execute the planned bone resection and implant positioning plan with a high level of accuracy. Existing reports comparing CO THA versus RO THA have shown conflicting outcomes [6, 14, 15, 20, 22]. Initial studies found RO THA was associated with improved functional outcomes as assessed using the Harris ship score, increased accuracy of acetabular implant positioning, better preservation of acetabular bone stock, improved restoration of native femoral offset, and reduced postoperative leg-length inequality compared to CO THA [6, 7, 9, 14, 15, 20]. However, further studies have shown no difference in CO THA versus RO THA with respect to functional outcomes, implant survivorship, and complications at short-term follow-up [4, 17, 19, 21]. Delays in the widespread implementation of RO THA have been attributed to the limited data showing any functional benefit with this procedure compared to an already established and highly cost-effective CO THA [7, 13].

Illgen et al. reviewed outcomes in 200 consecutive CO THAs followed by 100 consecutive RO THAs and found RO THA was associated with an additional 71% improvement in the accuracy of acetabular implant positioning compared with manual THA in the first year of use [9]. Acetabular implant positioning within Lewinnek’s safe zones (inclination, 30–50°; anteversion, 5–25°) was achieved in 30% of the first 100 consecutive CO THAs, 45% of the last 100 consecutive CO THAs, and 77% in the first 100 consecutive RO THAs (*p* < 0.001) [9]. Domb et al. conducted a retrospective radiological review of 50 patients undergoing CO THA versus 50 patients receiving RO THA [6]. All operative procedures were performed through the posterior approach. The study showed that all 50/50 (100%) RO THAs had acetabular cup positioning within Lewinnek’s safe zone compared to only 40/50 (80%) in the CO THA group (*p* = 0.001). Furthermore, 46/50 (92%) RO THAs had acetabular cup positioning within Callanan’s modified safe zone (inclination, 30–45°; anteversion, 5–25°) compared to only 31/50 (62%) in the CO THA group (*p* = 0.001). The odds ratio for an implanted acetabular cup out of Lewinnek’s safe zones was zero and Callanan et al. was 0.142 (95% CI 0.044–0.457). Nawabi et al. conducted a study on 12 cadaveric specimens that received CO THA on one side and RO THA on the contralateral side [20]. All procedures were performed using the posterior approach. The root-mean-square error for manual implantation was five times greater for acetabular cup inclination and 3.4 times greater for acetabular cup anteversion compared to robotic-arm assistance (*p* < 0.01). Tsai et al. conducted a retrospective study in which 12 patients undergoing RO THAs and 14 patients undergoing CO THAs had postoperative CT scans to assess implant positioning [25]. This study found that there was increased combined anteversion of 19.1 ± 11.7° in the RO THA group compared to 23.5 ± 23.6° in the CO THA group (*p* < 0.001). Cup inclination decreased by 16.5 ± 6.0° in the robotic THA group compared to 10.2 ± 6.8° in the CO THA group (*p* < 0.001).

The main limitations of existing studies comparing CO THA versus RO THA are that they are based on cadaveric specimens or retrospective clinical trials with limited data on functional outcomes, radiological results, or complications [6, 7, 9, 14, 15, 20]. Within each treatment group, different preoperative imaging modalities were used for surgical planning, operative procedures were performed with varying implant designs, and postoperative rehabilitation was not standardised. Observers recording outcomes were not blinded to the treatment group, and follow-up of outcomes and complications within each treatment group was limited to the early postoperative period [6, 7, 9, 14, 15, 20]. There is a need for high-quality evidence comparing CO THA versus RO THA. It is possible to improve on these previous studies by using the same preoperative planning technique in both treatment groups, prospectively randomising study patients to the treatment groups, and collecting data on a more comprehensive and robust range of clinical, functional, and radiological outcomes. All operative procedures will be undertaken using the standard posterior approach, sitting and standing spinopelvic radiographs will be used to assess patient-specific functional pelvic kinematics, and identical implant designs will be used in both treatment groups, which will help to blind observers recording radiological outcomes. The findings of this study will enable an improved understanding of differences in CO THA versus RO THA with respect to patient satisfaction, functional outcomes, implant survivorship, cost-effectiveness, and complications.

## Methods/design

### Objectives

The primary objective of this study is to compare the accuracy of achieving the planned centre of hip rotation in CO THA versus RO THA. This will be assessed within each treatment group by measuring the difference in the achieved centre of rotation on postoperative CT scanogram compared to the planned centre of rotation on preoperative pelvic CT scan. The study hypothesis is that RO THA will improve the accuracy of achieving the planned centre of rotation compared to CO THA.

The secondary objectives are to compare the following outcomes between the two treatment groups:
Accuracy of achieving planned component positioningAccuracy of restoring planned hip biomechanicsSpinopelvic functional kinematicsSurgical efficiencyPostoperative functional rehabilitationFunctional outcomesQuality of lifeRange of motionResource use and cost-effectivenessComplications

Specific study outcomes related to the primary and secondary objectives are discussed in the “Outcomes” section below.

### Trial design

This study is a prospective, single-centre, randomised controlled trial. The study will be undertaken in the Department of Trauma and Orthopaedics, University College Hospital, [name]. The study will include 60 patients randomly allocated to either CO THA (control group) or RO THA (investigation group). The study commenced patient recruitment in December 2018 and is expected to complete patient recruitment in December 2020. All patients will be followed up for 2 years after surgery, and therefore, the anticipated completion date for the study is December 2022. The study is sponsored by University College London, UK. The patient enrolment flow chart is presented in Fig. 1. The schedule of enrolment, interventions, and assessments for all study patients is shown in Fig. 2.

**Fig. 1 Fig1:**
[figure not shown]
Patient enrolment flow chart

**Fig. 2 Fig2:**
[figure not shown]
Schedule of enrolment, interventions, and assessments for all study patients

### Eligibility criteria

The inclusion criteria for this study are as follows: patient has symptomatic hip osteoarthritis requiring primary THA, patient fit for surgical intervention following review by surgeon and anaesthetist, patient aged between 18 and 80 years at time of surgery, patient able to give informed consent and agrees to comply with the postoperative review programme, and patient has sufficient mobility to attend follow-up clinics. The exclusion criteria for this study are as follows: patient undergoing revision surgery or second-stage THA, patients in whom the planned hip biomechanics are in a different position to the contralateral hip (e.g. developmental dysplasia of the hip or protrusio acetabuli), patient not suitable to have the planned study implants (e.g. requiring dual mobility component or cemented implants), patient had previous contralateral THA, patient is immobile or has another neurological condition affecting musculoskeletal function, patient already enrolled on another concurrent clinical trial, patient unable or unwilling to sign the informed consent form specific to this study, and patient unable to attend the study follow-up programme.

### Recruitment

Patients will be recruited from the orthopaedic outpatient clinic at University College Hospital, London, UK. All patients will be screened by the clinical team (orthopaedic consultant surgeon, clinical research fellow, and orthopaedic registrar) for study participation based on the predefined inclusion and exclusion criteria listed above. Patients that fulfil the eligibility criteria and express an interest to participate in the study will be provided with an ethics committee-approved patient information sheet. This provides details about the study treatment, follow-up, and contact details for further information. All members of the clinical team are familiar with the study and will address any preliminary questions about the study. Details of those patients expressing an interest to participate in the study will be recorded in the patient contact form and forwarded to the research physiotherapist. The research physiotherapist will phone the patient 4 weeks after this consultation to discuss any further questions and confirm if the patient would like to participate in the study.

### Consent

Informed consent will be obtained by the chief investigator or principal investigator when the patient attends for the preoperative planning CT scan. This is 6 weeks after the outpatient consultation for agreement to THA and 2 weeks before surgery. It is important to the data collection scheme that patients are able to follow commands, read, and interpret questions via questionnaires. For those who cannot hear, read, or understand English, an interpreter will be provided. The consent form describes the benefits and complications associated with THA and details additional risks associated with participation in this study, including additional radiation exposure (equivalent to two plain radiographs) compared to routine (non-research) patients undergoing THA. The consent form also explains that patients are free to withdraw from the study at any timepoint without their medical or legal rights being affected, their medical notes will be reviewed by the research team, and their general practitioners will be informed of their participation in the study.

### Allocation

After informed consent has been obtained, the research physiotherapist will randomise the patient into one of the two treatment groups using an online random number generator (www.random.org). A number from 1 to 60 can be randomly generated and will allocate a patient to one of the two arms of the study: 1–30 inclusive for the control group, 31–60 inclusive for the investigation group. The research physiotherapist will perform the randomisation procedure and store the designated treatment group for each patient on a password-encrypted file on the hospital computer. The operating surgeon will have this information communicated to him on the morning of surgery.

### Preoperative imaging

All patients will undergo preoperative imaging with sitting and standing spinopelvic radiographs, pelvic and hip radiographs, and CT scan of the pelvis and proximal femur. Preoperative templating will be undertaken by the operating surgeon. In both treatment groups, pelvic radiographs will be exported onto Traumacad software (Traumacad, Petach-Tikva, Israel) to template implant positioning and sizes for achieving the planned bone coverage, horizontal and vertical centres of rotation, acetabular and femoral offset, and leg-length correction. In all patients, the pelvic CT scan will be uploaded onto a computer software programme (Mako Surgical, Kalamazoo, MI, USA) to create a patient-specific CAD model of the patient’s osseous anatomy. The operating surgeon will use this virtual three-dimensional reconstruction to plan the operative procedure to restore the patient’s native hip biomechanics as guided by the contralateral side. In both treatment groups, the surgical objectives will be to restore the native horizontal and vertical centres of rotation, reproduce the native combined offset, restore natural femoral and acetabular version and inclination within Lewinnek’s and Callanan’s safe zones, and fully correct any pre-existing leg-length discrepancy. The computer robotic software will be used to calculate the required acetabular bone reaming, femoral osteotomy site, implant size, and implant positioning for achieving these surgical objectives.

### Surgical intervention

In patients undergoing CO THA, the femoral osteotomy site will be marked using the patient-specific CAD using measurements from the greater and lesser trochanters with the femoral neck cutting guide in place. An oscillating saw will be used to perform the osteotomy with Hohmann retractors protecting the surrounding soft tissues. The femoral osteotomy will be performed with the saw blade 45° to the femoral shaft and in the plane of the tibia. An entry point will be created in the proximal femur using a box chisel, with sequential reaming until contact with the cortical bone is felt, and then progressively larger raspers inserted into the proximal femur while maintaining the planned femoral version. Rasps will be used until the point where stability can be achieved with the definitive components. Sharp Hohmann retractors will be positioned over the anterior wall to lever the femur anteriorly and under the transverse acetabular ligament to expose the whole acetabulum for preparation. Soft tissues overhanging the acetabular circumference will be excised. Osteophytes will also be excised with an osteotome and the medial wall visualised. Sharp, hemispherical reamers will be used to remove the residual acetabular cartilage and expose the underlying subchondral bone. Reamers will be sequentially increased in size until the planned depth is reached. An external alignment guide will be attached to the cutting-edge reamer handle and acetabular impactor to improve the accuracy of acetabular cup positioning. The transverse acetabular ligament will be used as a fixed internal anatomical landmark for accurate positioning of the acetabular component within the safe zones of Lewinnek et al. and Callanan et al. to optimise stability and reduce the risk of dislocation. Any residual osteophytes will be removed at this stage using an osteotome and bone nibbler, and the trial prosthesis inserted to ensure satisfactory coverage and stability. Line-to-line technique for acetabular implantation will be used with implantation of the acetabular cup that is the same size as the last reamer used, and this will be augmented with two acetabular screws. The final femoral stem will then be implanted, femoral head applied to the taper, and hip reduced. The adjustment to a shorter or longer head can be performed at this stage.

In patients undergoing RO THA, three threaded registration pins will be inserted into the iliac crest for the attachment of the fixed pelvic array. One large screw will be inserted into the junction of the intertrochanteric ridge and lesser trochanter for the attachment of the femoral array, and a femoral checkpoint will be inserted just anterior to the greater trochanter. Femoral registration will be undertaken by registering and verifying the position of patient-specific anatomical landmarks displayed on the screen. Intraoperative measurements in the coronal plane as described by Murray will be displayed throughout the procedure. The femoral osteotomy will be marked using the probe and the osteotomy performed using an oscillating saw blade with Hohmann retractors protecting the surrounding soft tissues. The femur will be prepared with a box chisel, sequential reamers inserted, and progressively larger rasps inserted using the planned femoral version. The final rasp will be left in position and the femoral version recorded. The pelvic checkpoint will then be positioned outside the acetabular cavity in the bone just superior to the acetabular rim. Acetabular registration will be undertaken by registering and verifying the position of osseous landmarks displayed on the screen. The acetabular position and orientation may be fine-tuned based on intraoperative data on femoral version and inclination. The RIO robotic arm interactive orthopaedic system (Mako Surgical Corporation, Kalamazoo, USA) will be used to guide acetabular bone reaming within the confines of the haptic tunnel and implant the acetabular component into its final position and orientation as defined in the surgical plan. The final stem will then be implanted, trial head positioned onto the taper, and hip reduced. The femoral array will be inserted into the femoral screw, and the leg-length and offset change shown on the screen. The adjustment to a shorter or longer head can be performed at this stage.

All surgical procedures will be performed under the direct supervision of a single surgeon using the standard posterior approach. Trial implants will be used to assess hip stability, offset, soft tissue tension, and leg-length discrepancy prior to implantation of the permanent acetabular and femoral components in both treatment groups. Patients in both treatment groups will receive the standard or high-offset Accolade II femoral stem (Stryker Ltd., Mahwah, NJ, USA) and the trident acetabular shell (Stryker Ltd., Mahwah, NJ, USA). Patients in both treatment groups will undergo standardised inpatient and outpatient rehabilitation programmes. This will include six outpatient physiotherapy sessions at two-weekly time intervals. Patients will receive physiotherapy-supervised closed and open chain exercises to transition through four phases of rehabilitation with predefined milestones relating to the following: core strength and stability, lower limb proprioception, muscle strengthening, hip and knee range of motion, mobility with and without walking aids; ascending and descending stairs; and functional activities to return to pre-disease level of activity. Any deviations from the standardised proforma will be recorded and presented with the study findings.

### Outcomes

All study patients will undergo review by two observers (one orthopaedic registrar and one clinical research fellow) at 6 weeks, 6 months, 1 year, and 2 years following surgery. During these follow-up times, predefined clinical, functional, and radiological outcomes will be recorded by these observers using case report forms (CRFs). The following outcomes will be recorded in all study patients:
Accuracy of achieving the planned implant positioning and hip biomechanics (horizontal centre of rotation, vertical centre of rotation, acetabular offset, femoral offset, and leg-length discrepancy) as assessed using CT scanograms performed postoperatively at 6 weeksOperating time (minutes)Time to hospital discharge (hours)Analgesia requirements during inpatient admission and postoperatively at 6 weeks, 6 months, 1 year, and 2 yearsPatient-reported outcome measures including Oxford hip score (OHS), Harris hip score (HSS), Hip disability and osteoarthritis outcome score (HOOS), University College Hospital hip (UCH) score, Western Ontario and Mcmaster Universities Osteoarthritis Index (WOMAC), and University of California at Los Angeles hip (UCLA) score preoperatively and postoperatively at 6 weeks, 6 months, 1 year, and 2 years following surgeryHealth-related quality of life as measured using European Quality of Life questionnaire with 5 dimensions for adults (EQ-5D) preoperatively and postoperatively at 6 weeks, 6 months, 1 year, and 2 yearsMobilisation distance (metres) and use of mobility aids during inpatient admission and postoperatively at 6 weeks, 6 months, 1 year, and 2 yearsRange of movement (degrees) in the hip joint in the supine position as assessed with a goniometer during inpatient admission and postoperatively at 6 weeks, 6 months, 1 year, and 2 yearsResource use and cost-effectiveness including comparisons between the two treatment groups relating to operating time, theatre efficiency, equipment and sterilisation costs, analgesia requirements, inpatient rehabilitation, time to discharge, outpatient follow-up, additional imaging costs, and need for further surgeryComplications

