### Blinding

It is not possible to blind study patients as RO THA is associated with an additional incision over the iliac crest for insertion of the acetabular registration pins. However, all observers recording radiological outcomes will remain blinded to the treatment group. Study patients will be identifiable with a unique study number. Only the research physiotherapist will have the key to identify individual patients and their respective treatment arm. Any documents related to the study will be archived directly at the study site by the research physiotherapist within a locked filing cabinet in a locked research office. This office has swipe card access with on-site security and 24-h CCTV surveillance. Patient data will be logged electronically using each patient’s unique identification number with computer software on an encrypted, password-protected research computer.

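### The two observers who examine every patient also record the primary CT outcome, so the promised blinding of that outcome is not protected as written

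*Protocol article*

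**What the plan says.** All statements are in the protocol article.

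- **Primary endpoint (Objectives).** The stated method is "measuring the difference in the achieved centre of rotation on postoperative CT scanogram compared to the planned centre of rotation on preoperative pelvic CT scan". Outcomes places this CT scanogram at 6 weeks.
- **Who sees the patients (Outcomes).** The text reads "All study patients will undergo review by two observers (one orthopaedic registrar and one clinical research fellow) at 6 weeks, 6 months, 1 year"; a further review follows at 2 years. The outcomes listed include hip range of movement, taken supine with a goniometer, at each of these visits.
- **Who records the images (Outcomes).** At the same follow-up times, "predefined clinical, functional, and radiological outcomes will be recorded by these observers using case report forms (CRFs"). The phrase refers back to the same two people.
- **The promise (Blinding).** "all observers recording radiological outcomes will remain blinded to the treatment group".
- **The visible sign (Blinding).** Patients cannot be blinded because "RO THA is associated with an additional incision over the iliac crest for insertion of the acetabular registration pins".
- **Safeguards.** Background says that "identical implant designs will be used in both treatment groups, which will help to blind observers recording radiological outcomes". Blinding adds a unique study number for each patient and says that "Only the research physiotherapist will have the key to identify individual patients and their respective treatment arm".

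**The concern.** One section gives patient examination and radiological recording to the same two people. The next says that whoever records radiological outcomes is blinded, and in the same paragraph names a physical sign of allocation on the patient. An observer who examines the hip of a supine patient at 6 weeks may see the extra incision, or may be told the allocation by a patient who knows it.

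The primary endpoint is at stake. It is a distance in millimetres with a planned difference of 0.8 mm, and the hypothesis favours the robotic arm. Background also criticises earlier comparisons because their observers were not blinded, so blinded radiological reading is one of the improvements this trial claims. If the readers know the arm, the trial loses that advantage on its main outcome.

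**Working it through.** **Step 1. Set the sections side by side.**

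| Question | Answer in the protocol article | Section |
|---|---|---|
| Who reviews patients at 6 weeks? | The two observers | Outcomes |
| Does that review involve examining the hip? | Yes, supine range of movement by goniometer | Outcomes |
| Who records radiological outcomes? | The same two observers | Outcomes |
| When is the primary CT done? | 6 weeks | Outcomes |
| Can the arm be seen on the patient? | Yes, extra iliac-crest incision in the robotic arm only | Blinding |
| Are radiological recorders blinded? | Yes, all of them | Blinding |

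**Step 2. Test each safeguard against the incision.**

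- Identical implants make the prostheses look alike on the image. They do not change what is seen on the patient.
- A study number conceals the arm only from someone who has not connected the number with a patient. Both observers meet every patient and complete that patient's forms.
- A key held by the research physiotherapist protects the allocation list. It does not stop an observer from seeing the incision or a patient from mentioning it.

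None of the three closes the route from examination to reading. The article describes no separate CT reader, no fresh coding of images and no reading apart from the clinic visits.

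**Step 3. Reproduce the plan's sample size, as the setting for an illustration.** Inputs from Sample size: means 3.7 and 2.9 mm, SD 1.0 mm, two-sided 5%, power 80%.

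- Effect size: (3.7 − 2.9) / 1.0 = 0.8.
- The exact two-sample t test needs 25.52 per arm, so 26 per arm and 52 in total, as stated. Power at 26 per arm is 80.7%.
- With 10% attrition, 52 / 0.9 = 57.8, rounded up to 58. The planned 60 covers this.

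The concern changes none of these figures.

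**Step 4. Illustrate what unblinded reading could do.** Suppose there is no true difference and knowledge of the arm shifts the mean reading in one arm by b mm. The two-sided t test then has noncentrality b / (SD × √(2/n)) on 2n − 2 = 50 degrees of freedom. With n = 26 and SD = 1.0, √(2/26) = 0.277.

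| Assumed shift b (mm) | Share of planned 0.8 mm | Noncentrality | Probability of p < 0.05 |
|---|---|---|---|
| 0 | 0% | 0 | 5% |
| 0.1 | 12.5% | 0.36 | 6.4% |
| 0.2 | 25% | 0.72 | 10.9% |
| 0.3 | 37.5% | 1.08 | 18.6% |

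Every value of b is an assumption. At 0.1 mm the effect is slight. At a quarter of the planned difference the error rate has about doubled.

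**The case against.** The best defence is that the article makes an explicit commitment to blinded radiological recording and does not say who measures the scans, in what order or under what code. Recording a result on a form is not necessarily measuring it. Such logistics often sit in the full protocol, which is not shown. CT measurement is also less open to influence than a clinical score.

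Much of this stands, and it limits the point. A reader might infer that the blinding fails, or that the primary result will be biased. The documents do not support that: seeing the incision is a strong inference but not a stated fact, and no text says that a scan is read straight after the patient is examined.

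Three further inferences also go too far:

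- **The observers belong to the treating team and so know the arm.** Recruitment says "All patients will be screened by the clinical team (orthopaedic consultant surgeon, clinical research fellow, and orthopaedic registrar", but that describes screening before randomisation and lists roles, not individuals. Allocation names only the operating surgeon as being told the arm.
- **Pin tracks on the CT give the arm away.** Nothing in the article describes what the scanogram shows or covers.
- **Blinded reading is the only protection.** Planning uses the same CT software in both arms, the surgeon learns the arm only on the morning of surgery, and a blinded observer does the analysis. These measures protect the plan and the analysis, but not the reading of the postoperative scan.

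The defence does not remove the inconsistency. An article may leave out coding details, but this one positively assigns examination and radiological recording to the same people while promising that those people are blinded.

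**Conclusion.** The point holds as an unreconciled pair of statements bearing on the primary endpoint: followed as written, the plan leaves the 6-week CT reading open to observers who may know the arm, and no stated safeguard prevents it. This rests on two readings of the text: that the phrase in Outcomes refers to the two reviewing observers, and that a supine hip examination can expose an iliac-crest incision or prompt a patient to mention it.

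The text shows unprotected blinding. It does not show that bias occurs. The illustrative false-positive rates of about 6%, 11% and 19% depend wholly on assumed shifts of 0.1, 0.2 and 0.3 mm. The sample size is unaffected.

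**What to change.** Reconcile the Outcomes and Blinding sections, using one of two arrangements:

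1. **Coded batch reading.** The research physiotherapist, who already holds the key, gives each CT a random image code unlinked to the study number. The CTs are read in batches, away from the clinic visits and without patient identifiers.
2. **Split roles.** One observer examines patients and the other only reads CTs. The Outcomes sentence must then change, because at present both observers review all patients and neither is free of patient contact.

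In either case, lock the readings before linking them to arm, and say plainly in Blinding that clinical and functional outcomes are not observer-blinded.

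The cost is small. Under the first arrangement 60 scans need recoding and CT results come later. The second uses the existing two observers but gives up review of each patient by both. Neither changes the sample size or treatment. The first leaves some residual risk, since its readers will have met the patients, but it breaks the direct link between a scan and a remembered patient.
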